### Sample size considerations

Conform Kallmes et al. [18], we expect a 1.5 point difference in pain relief as measured by VAS score. Given that there are seven measurement points (α = 0.05 and β = 0.20) we need 142 patients in total). Assuming a withdrawal rate of 20%, a total of 180 patients will be enrolled, 90 in each group. We used G-Power to calculate the sample size.

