### Statistical analysis

The data will be analysed according to the intention-to-treat principle. Standard statistical techniques will be used to describe characteristics of patients in both groups. We will compare baseline characteristics in the two treatment groups and if incomparability appears, we will in secondary analysis, adjust for differences. The primary outcome, significant pain relief, will be compared between groups using analysis of variance for repeated measures. If adjustment for possible baseline incomparability is needed, analysis of covariance will be done. Since we expect that the difference between the two groups will become evident from 3 months onwards, the analysis will also be performed only using scores before and 3, 6, and 12 months after the procedure.

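### The primary ANOVA counts the pre-procedure VAS among its repeated outcomes and plans adjustment only if imbalance appears; this is valid but inefficient, and baseline VAS should be a fixed covariate

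*Protocol article*

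**What the plan says.** The Clinical follow-up section schedules the VAS once before the procedure and six times after it (1 day, 1 week, and 1, 3, 6 and 12 months). Sample size considerations opens its calculation with "Given that there are seven measurement points". The Statistical analysis section compares the primary outcome by repeated-measures ANOVA and adds an analysis "only using scores before and 3, 6, and 12 months after the procedure". It does not say whether the group or the group-by-time term is tested.

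The same section mentions adjustment twice. First, for baseline characteristics: "if incomparability appears, we will in secondary analysis, adjust for differences". Then, directly after the sentence on the primary outcome: "If adjustment for possible baseline incomparability is needed, analysis of covariance will be done". Neither sentence says what counts as incomparability or which covariates would enter.

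**The concern.** A score taken before the procedure cannot carry a treatment effect. Kept as an outcome, it adds noise to a group comparison, or spends its information inefficiently in an interaction test. Used as a covariate, the same score would remove variance from the follow-up comparison.

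Tying adjustment to observed imbalance forgoes that gain when the groups look balanced, and leaves room to choose a model after the baseline table is seen. At stake are the power and clarity of the primary test.

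**Working it through.** **Inputs from the protocol article.** Effect: "we expect a 1.5 point difference in pain relief as measured by VAS score". Size: "Given that there are seven measurement points (α = 0.05 and β = 0.20) we need 142 patients in total", so 71 per arm. Enrolment: "Assuming a withdrawal rate of 20%, a total of 180 patients will be enrolled, 90 in each group". Follow-up schedule as above; VAS range 0 to 10.

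**Assumptions, since the document gives none.** Two-sided α; common SD; equal correlation r between any two measurements; a difference of 0 at baseline and 1.5 at every later visit.

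**1. The plan's own figure.** 142 / 0.80 = 177.5, i.e. 178, consistent with 180. The 142 itself cannot be reproduced without an SD or correlation. With effect size f = 1.5 / (2 × SD), the between-group repeated-measures formula with seven points returns 142 at f = 0.18, r = 0.5 (SD about 4.2) and at f = 0.15, r = 0.3 (SD about 5.0). So 142 is attainable but not verifiable, and is not shown to be wrong.

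**2. Is baseline an outcome?** 1 before + 6 after = 7. The stated seven points are reached only by counting the pre-procedure score, and the restricted analysis names that score explicitly.

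**3. If the group main effect is tested.** The expected contrast is 1.5 × 6/7 = 1.29 points. In the restricted analysis (one before, three after) it is 1.5 × 3/4 = 1.125 points.

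**4. Power on one benchmark.** Choose the SD so that 142 patients give exactly 80% power for 1.5 points at all seven measurements. The variance is unchanged and the effect is 6/7 as large: Φ(2.80 × 6/7 − 1.96) = Φ(0.44) = 67%, whatever r is.

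**5. Baseline as covariate, mean of the six follow-up scores.** The variance factor is (1 + 5r)/6 − r², against (1 + 6r)/7 for the seven-point mean. Power = Φ(2.80 × √ratio − 1.96), where ratio is the seven-point factor divided by the adjusted factor:
- r = 0.3: 0.400 / 0.327, power 87%
- r = 0.5: 0.571 / 0.333, power 96%
- r = 0.7: 0.743 / 0.260, power 99.7%

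**6. If group-by-time is tested.** The noncentrality is (71/2) × 1.5² × (6/7) / [SD² (1 − r)] on 6 and 840 df.

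**7. Sensitivity to the SD.** The first three rows are the benchmark of step 4; the others assume an SD.

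| SD | r | Seven-point main effect | Seven-point group-by-time | Follow-up mean, baseline-adjusted |
|---|---|---|---|---|
| 5.0 | 0.3 | 67% | 26% | 87% |
| 4.2 | 0.5 | 67% | 52% | 96% |
| 3.7 | 0.7 | 67% | 89% | 99.7% |
| 3.0 | 0.3 | 98% | 68% | 99.9% |
| 3.0 | 0.5 | 92% | 85% | 99.9% |
| 3.0 | 0.7 | 84% | 98% | >99.9% |
| 2.5 | 0.3 | 99.8% | 86% | >99.9% |
| 2.5 | 0.5 | 98% | 96% | >99.9% |
| 2.5 | 0.7 | 94% | 99.9% | >99.9% |

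**8. Direction without any SD.** The seven-point group contrast is proportional to the follow-up mean plus one sixth of baseline. Change from baseline subtracts baseline with coefficient 1. ANCOVA estimates the coefficient that minimises variance. Randomisation makes the expected baseline difference zero, so ANCOVA is at least as efficient as either, apart from one degree of freedom.

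**9. Type I error** (40,000 simulated trials, r = 0.5, main effect): fixed unadjusted model 5.0%; fixed ANCOVA 5.0%; switching to ANCOVA only when a baseline test gives p < 0.05, 3.4%; reporting the better of the two, 8.7%.

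**The case against.** **Dilution depends on the tested term.** The outcome is pain relief, which suggests change from the pre-procedure score; with baseline as a level of the time factor, group-by-time expresses that change undiluted. This stands. A reader might infer that the effect is diluted in any case, but the article does not name the term.

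**The primary model may be fixed.** The first adjustment sentence confines adjustment to secondary analysis, and the ANCOVA sentence may only name the method for it. This largely stands. A reader might infer that the data choose the primary model, or that type I error is inflated. The documents do not support either: the fixed unadjusted model holds 5.0%, and the 8.7% requires picking the better result, which is not planned. What remains is an ambiguity, because the later sentence does not repeat the restriction.

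**Baseline VAS as both outcome and covariate** is another tempting inference. No covariate is named, so it is conjecture.

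**The 67% rests on an SD that is hard to credit.** On a 0 to 10 scale the SD cannot exceed about 5. Patients are approached only with a VAS of five or more, and scores confined to 5 to 10 have an SD of at most about 2.5. The back-solved 5.0 and 4.2 are therefore implausible at baseline. This stands; the 67% is conditional, not a finding about the trial.

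**The constant effect is an assumption.** The Background hypothesises less pain at every visit, but the Statistical analysis section expects the difference from 3 months onwards. If 1.5 points appear only at 3, 6 and 12 months, the six-visit mean carries 1.5 × 3/6 = 0.75 and the seven-point main effect 1.5 × 3/7 = 0.64. On the benchmark SDs the adjusted mean then has 34%, 45% and 66% power at r = 0.3, 0.5 and 0.7, still above the main effect's 22%. The group-by-time noncentrality doubles (3 × 4/7 replaces 6 × 1/7), giving 52%, 86% and 99.7%. So the advantage over group-by-time holds under a constant effect only. That is a reason to name the term; a baseline-adjusted model can carry a treatment-by-visit term too.

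**Conclusion.** The point holds as one of efficiency and clarity. Baseline VAS is a level of the repeated outcome and never a planned covariate, and the trigger for adjustment has no criterion. The planned test is valid.

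For a group main effect the expected contrast falls to 6/7 of its size, or 3/4 in the restricted analysis, and the direction of the loss needs no assumed SD or correlation. For group-by-time the loss is one of power, and only under a constant effect. How much power is lost cannot be settled from the document: main-effect power is 67% on the back-solved benchmark, and about 94% or more at an assumed SD of 2.5 with r from 0.3 to 0.7. The figures do not show that the trial is underpowered or that 142 is wrong. The change is worth making because it is nearly free.

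**What to change.** In the Statistical analysis section:
- Use only post-procedure VAS scores as outcomes, both in the primary model and in the 3, 6 and 12 month analysis.
- Include baseline VAS as a prespecified covariate in both, whatever the observed balance.
- Name the treatment term that is tested, and check it against the expected timing of the effect.
- Delete the imbalance trigger, and keep adjustment for other baseline characteristics as one prespecified secondary analysis with its covariates listed.

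Baseline VAS is already collected, so the cost is a few sentences and one degree of freedom.

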The most important differences between the two sham studies and VERTOS II is patient selection. In the sham studies both acute and chronic fractures were included while in VERTOS II only acute fractures were eligible. In addition, bone edema in the affected vertebra was not a consistent inclusion criterion in the sham studies. The sham studies lacked a control group without intervention. The discordant results from the sham studies, on the one hand, and VERTOS II, on the other hand, have incited much debate [20-24]. Apparently clinicians do still not know how to best treat their patients. The objectives of this study is to evaluate the efficacy of bone cement injection in PV for patients with acute painful osteoporotic compression fractures, as compared with a simulated placebo procedure without injection of bone cement. We hypothesize that patients who had undergone PV would report less pain at 1 day, 1 week and 1, 3, 6 and 12 months (the primary outcomes) than those in the sham control group. In addition, we hypothesize that the back pain related disability is less and the quality of life (QOL) is better of patients undergoing PV compared with patients in the simulated placebo condition

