### Clinical follow-up

An experienced nurse-practitioner requests patients to complete a standard questionnaire before and at 1 day, 1 week, and 1, 3, 6 and 12 months after the procedure. The questionnaire consist of the VAS score and questions about use of pain medication, pain location, and pain type (primary outcomes). The VAS score is a pain score ranging from 0 (no pain) to 10 (worst pain ever) [26] Questions concerning use of pain medication, pain location, and pain type are included. Secondary outcomes are back pain related disability and QOL as measured with the Roland Morris Disability (RMD) Questionnaire and the Questionnaire of the European Foundation for Osteoporosis (Qualeffo), respectively. The Qualeffo is developed specifically for patients with osteoporosis [27]. This questionnaire consists of 41 questions about: pain, physical function, social function, general health perception, and mental function. The Qualeffo score ranges from 0 (best quality of life) to 100 (worst quality of life). This questionnaire will be completed at five measurement moments (before and at 1, 3, 6, and 12 months after the procedure). The RMD questionnaire is a disability questionnaire that measures the functional status of patients with back pain [28,29]. The RMD will be completed at all measurement points. Patients visit the internist at 1, 3, 6 and 12 months follow-up. Patients receive a pain diary. Patients are asked to complete the VAS score and use of analgesics is recorded on a daily basis during the first month after randomization.

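### The stated 80% power is attached to no identified test or time profile: the hypothesis claims less pain from day 1, the analysis section expects a difference from 3 months, and two unranked analyses follow

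*Protocol article*

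**What the plan says.** Three sections of the protocol article bear on this point.

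- **Hypothesis (Background).** "We hypothesize that patients who had undergone PV would report less pain at 1 day, 1 week and 1, 3, 6 and 12 months". These visits are labelled the primary outcomes.
- **Analysis (Statistical analysis).** The primary outcome is compared by repeated-measures analysis of variance. The section does not say whether the group main effect or the group-by-time interaction decides the comparison. It continues: "Since we expect that the difference between the two groups will become evident from 3 months onwards". On that ground it repeats the comparison on the pre-procedure, 3-month, 6-month and 12-month scores alone.
- **Sample size (Sample size considerations).** "we expect a 1.5 point difference in pain relief as measured by VAS score", in line with a cited sham-controlled trial. "Given that there are seven measurement points (α = 0.05 and β = 0.20) we need 142 patients in total". Allowing for one patient in five to withdraw, the section sets enrolment at 180, or 90 per arm. The software is G-Power. No SD, within-patient correlation or test is given.

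The Clinical follow-up section has the questionnaire completed "before and at 1 day, 1 week, and 1, 3, 6 and 12 months after the procedure". The seven measurement points are therefore one pre-procedure score and six follow-up scores.

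**The concern.** The Background expects a benefit at every visit from the first day. The Statistical analysis section expects it to show from 3 months. The sample size adopts neither profile: it takes a single 1.5-point difference and attaches it to no visit. The Background places the primary outcomes of the trial cited for the 1.5 points at 1 month, which is before the difference is expected to show here.

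The count of seven includes a score taken before treatment, where randomisation implies no group difference. In a repeated-measures ANOVA with that score as an outcome level, a treatment effect over follow-up is split between the group effect and the interaction. The choice of effect therefore decides the power.

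Two things are at stake. A real late benefit could be reported as no effect if the deciding test averages over visits where little was expected. And with two unranked analyses of the primary outcome, the one to emphasise could be chosen after the data are seen.

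**Working it through.** **Inputs from the document:** difference 1.5 points; α = 0.05 (taken as two-sided); power 80%; 142 evaluable patients (71 per arm); 20% withdrawal; 180 enrolled; seven measurements, one of them baseline. **Assumed, because not stated:** equal variances, compound symmetry, and within-patient correlation ρ of 0.3 to 0.7.

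**1. The plan's own figures.** 142 / 0.80 = 177.5, so 178, and 180 is a reasonable rounding. The 142 cannot be reproduced without an SD, a correlation and a test. Several quite different calculations fit it:
- a two-sided t-test with SD 3.17;
- a between-group repeated-measures test over seven points with SD 5.0, 4.2 or 3.7 at ρ = 0.3, 0.5 or 0.7;
- approximately, a t-test at α = 0.05/7 with SD 2.5 (N = 144 by the t distribution, 140 by the normal approximation; power 79.9% with 71 per arm).

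**2. Group main effect over seven points, difference only at 3, 6 and 12 months.** With 71 per arm, 80% power corresponds to a standardised difference of 0.473 in the tested mean. The late-only seven-point average is 1.5 × 3/7 = 0.643 points.
- *Calibration A, 1.5 points at all seven points:* SD of the patient mean = 1.5/0.473 = 3.17. Standardised late-only difference = 0.643/3.17 = 0.203. **Power 22%** (27% if all 180 were evaluable).
- *Calibration B, 1.5 points at the six follow-up visits:* the average is 1.5 × 6/7 = 1.286, so the SD of the mean = 1.286/0.473 = 2.72. Standardised late-only difference = 0.643/2.72 = 0.237. **Power 29%.**

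These two results do not depend on ρ.

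**3. Group main effect in the four-point analysis (before, 3, 6, 12 months).** The average difference is 1.5 × 3/4 = 1.125. The variance of a mean of m scores is σ²(1 + (m−1)ρ)/m. At ρ = 0.5:
- A: σ = 4.19; SD of the four-point mean = 4.19 × √0.625 = 3.31; standardised difference 0.340; power 52%.
- B: σ = 3.59; SD of the mean = 2.84; standardised difference 0.396; power 65%.

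Over ρ = 0.3 to 0.7 the ranges are 49-54% (A) and 61-67% (B).

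**4. Group-by-time interaction.** The noncentrality is (N/4) × 1.5² × S / (σ²(1−ρ)), where S is the sum of squares of the effect profile about its mean.
- Constant effect at the six follow-up visits: S = 6 × 1/7 = 6/7. Set this to 80% power.
- Effect only at the last three visits: S = 3 × 4/7 = 12/7, which doubles the noncentrality. **Power about 99%.**
- Four-point analysis: S = 3 × 1/4 = 3/4. Power about 84%.

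**5. Type I error if both group-effect analyses are read as confirmatory at 5%.** The four scores are a subset of the seven. Under compound symmetry the correlation of the two means is √(v₇/v₄), with v₇ = (1+6ρ)/7 and v₄ = (1+3ρ)/4. At ρ = 0.5 this is √(0.571/0.625) = 0.956. The chance that at least one test is significant under the null is about **6.9%, 6.4% and 6.0%** at ρ = 0.3, 0.5 and 0.7.

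**The case against.** A reader might infer that the trial simply does not deliver its 80% power. The document does not support that.

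- **The test is not named.** A difference in pain relief can be read as a difference in change from baseline. With the pre-procedure score as a level of time, that is the interaction, and a late-only effect then raises its power. This stands. What also stands is that the interaction responds to any difference in profile, so a significant result does not by itself show less pain after vertebroplasty.
- **The result depends on calibration.** The lowest figure credits the planners with a 1.5-point difference at baseline. The same calibration is the only source of a drop to 67% when the effect is present from day 1 and absent only at baseline; no such loss should be claimed. With assumed SDs of 2.0-3.5 and ρ of 0.3-0.7, instead of calibration to 142, late-only power ranges from 24% to 85% for the main effect and from 87% to 100% for the interaction. If 142 came from a correction over seven visits, power at each of 3, 6 and 12 months stays about 80%, although the document mentions no per-visit tests.
- **Becoming evident from 3 months need not mean zero before.** This is fair. The late-only profile is the extreme case, and a small early difference would soften the contradiction.
- **The extra analysis answers the late expectation, and ranking belongs in the SAP.** In part. The word for it suggests an addition, and its main-effect power is higher. But the protocol itself introduces this analysis, on a rationale at odds with its primary hypothesis. Under the main-effect calibrations it still falls short of 80%.
- **Multiplicity is modest.** Agreed. A figure near 13.5% arises only if both interaction tests are also read as confirmatory, which the document nowhere says.

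**Conclusion.** The point holds in conditional form. The protocol contradicts itself on when the difference is expected, counts a pre-treatment score among the measurements used for sizing, and leaves two analyses of the primary outcome unranked. Its 80% power cannot be verified, because it belongs to no stated test, visit or profile.

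For a 1.5-point difference confined to 3, 6 and 12 months, power with 142 patients runs from about 22-29% (main effect, seven points), through about 49-67% (main effect, four points), to about 99% (interaction, seven points). This rests on calibrating each type of test to 80% at N = 142, compound symmetry, ρ of 0.3-0.7 and no earlier effect. That spread, from one unstated choice, is the finding; no single figure in it is the trial's power. The type I error from reading both group effects as confirmatory is a smaller matter, at about 6-7%.

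**What to change.** 1. Reconcile the Background hypothesis and the Statistical analysis section to one expected time profile.
2. Name one confirmatory contrast: the mean VAS difference between groups over the chosen post-procedure visits, with baseline VAS as a covariate and not as an outcome level. This is directional, and baseline cannot dilute it.
3. Label the other analysis secondary.
4. Restate the power of the 142 evaluable and 180 enrolled patients for that contrast, giving the SD and correlation used and counting only post-procedure measurements.

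The sponsor should choose the visits and say why. The Interventions section withholds cross-over only up to 6 months, so the contrast must also state how 12-month scores after cross-over are handled. Nothing in the document settles whether that visit should be kept or left out.

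The cost is wording changes and one re-run of the power calculation. The restated power may be less favourable than 80%. No extra patients are needed for this change.

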## Conclusion

The VERTOS IV study is a RCT comparing PV with a sham intervention using strict inclusion criteria designed to assess pain relief in patients with an acute osteoporotic VCF with mid-term follow-up.
